**Methods:**

This randomized controlled trial assesses the long-term effects of increased maternal speech exposure on structural connectivity at 12 months of age (age adjusted for prematurity (AA)) and language outcomes between 12 and 18 months of age AA. Study participants (*N* = 42) will include infants born very preterm (24–31 weeks 6/7 days GA). Newborns are randomly assigned to the treatment (*n* = 21) or standard medical care (*n* = 21) group. Treatment consists of increased maternal speech exposure, accomplished by playing audio recordings of each baby’s own mother reading a children’s book via an iPod placed in their crib/incubator. Infants in the control group have the identical iPod setup but are not played recordings. The primary outcome will be measures of expressive and receptive language skills, obtained from a parent questionnaire collected at 12–18 months AA. The secondary outcome will be measures of white matter development, including the mean diffusivity and fractional anisotropy derived from diffusion magnetic resonance imaging scans performed at around 36 weeks postmenstrual age during the infants’ routine brain imaging session before hospital discharge and 12 months AA.

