Our aim is to establish whether a language intervention (treatment) administered in the NICU has the potential to promote healthy language and brain development in very preterm infants. To achieve this goal, we have designed an interventional randomized controlled trial (RCT) that will test the causal effect of increased exposure to maternal speech in the NICU on language outcomes and white matter development in infants born very preterm. Our first aim will assess the long-term effects of increased maternal speech exposure on an infant’s expressive and receptive language abilities measured at 12–18 months of age adjusted for prematurity (AA). We focus on these language abilities because they have been linked to language processing abilities that are known to be strong predictors of later academic outcomes [34–36]. We hypothesize that, compared to controls, infants in the treatment group will demonstrate more advanced language skills at 12–18 months AA. Our second aim will assess the effects of increased maternal speech exposure on an infant’s white matter development at ~ 36 weeks PMA and 12 months AA. Measuring white matter development at these two ages will allow us to assess whether possible immediate effects of increased maternal speech exposure on white matter development are sustained over the first year of life. We hypothesize that, compared to controls, infants in the treatment group will demonstrate changes in dMRI measures reflecting increased white matter development. Specifically, infants in the treatment group will demonstrate lower MD.

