## Methods

### Study design

To achieve these aims, we propose an RCT that will involve 42 very preterm infants born and cared for at Stanford’s Lucile Packard Children’s Hospital (LPCH). Enrollment is planned from November 2019 to December 2021. For infants who meet the inclusion criteria of gestational age at birth (GA) of 24-0/7 to 31-6/7 weeks, we will obtain informed consent and questionnaires about the family’s demographics and language from parents, and a speech recording from each mother. Infants will then be randomized to the treatment (T) or control (C) group. Infants randomized to either T or C group will receive standard medical care, with the exception that infants randomized to the T group will also receive the maternal speech intervention achieved by playing recordings of maternal voice via iPods placed in an infant’s incubator or open crib. Infants in the C group will have the same auditory setup to ensure that parents and clinical staff remain blinded to the group status. The duration of the intervention will begin once an infant gets transferred to the intermediate care nursery, indicating medical stability, and end once an infant has received their clinical MRI, which is part of the standard medical care at LPCH and is performed prior to hospital discharge (~ 36–38 weeks PMA). The long-term effects of the intervention will be assessed at 12 months and 18 months AA. At 12 months AA, infant participants will undergo a dMRI scan during natural sleep, and parents will complete the MacArthur-Bates Communicative Development Inventories (CDI): Words and Gestures Questionnaire [37]. At 18 months AA, parents will complete another CDI: Words and Gestures Questionnaire, the primary outcome assessment of language development (see Fig. 1).

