### Outcome assessment methods

The primary outcome is language development (domain) assessed through the MacArthur-Bates CDI (measure) at (metric) 18 months AA (time point), quantified as expressive and receptive language raw scores and aggregated as group means (aggregation). The secondary outcome is white matter development (domain) assessed through dMRI scans (measure) collected at (metric) two different time points (time point): (1) prior to hospital discharge (neonatal time point) and (2) at 12 months AA (1-year time point), quantified with the dMRI metric (MD) and aggregated as group means (aggregation).

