### Primary outcome: language development

#### MacArthur-Bates CDI

In order to measure language development and production, parents of infant participants will complete the CDI: Words and Gestures Questionnaire [46] at 12 months AA and 18 months AA via web form or mail form with guidance from a trained clinical research assistant. The CDI Words and Gestures Questionnaire is a parent checklist that evaluates both verbal and non-verbal communication, as well as some aspects of play. Split into two parts, “The Early Words” section examines infants’ intentional linguistic communication, understanding, vocabulary, and language-based social interactions, while the “Actions and Gestures” section gauges communicative gestures, play, and symbolic understanding. As these metrics of language development are related to measures of processing speed and predictive of later language outcomes, the CDI Words and Gestures Questionnaire will serve as our primary measure of language development.

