### Analysis plan

#### Power calculations

We calculated the sample size based on power. The significance level is *p* < 0.05 for all analyses. Power estimates are based on the means, standard deviations, and samples size from an RCT neuroimaging study of preterm neonates that showed a significant effect of a parent-based NICU intervention on diffusion metrics measured at close-to-term age (Cohen’s *d* = 1.03) and developmental outcomes (Cohen’s *d* = 1.77) measured at 9 months AA [56]. Thus, if we assume an effect size that is more conservative than this earlier study, specifically Cohen’s *d* = 1.0, we will have a power of ß = 0.8, if we enroll a sample size of at least 17 participants per group. Therefore, our planned enrollment of 21 participants per group will yield a power of ß = 0.88 to detect an effect size at that level (Cohen’s *d* = 1.0). If our effect size is even smaller than we anticipate, for example, Cohen’s *d* = 0.9, a planned enrollment of 21 per group will still yield a power greater than 0.8 to detect a treatment effect.

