#### Analytic strategy

We anticipate that stratification prior to randomization will result in a close matching of T and C groups on demographic and health variables. Prior to statistical analyses, we will use independent samples t-tests (continuous variables) or chi-square tests (categorical variables) to assess the statistical balance between T and C groups on the basis of GA, sex, SES, clinical complications associated with premature birth, and language exposure during treatment and after hospital discharge. Analyses will use an intention-to-treat strategy [57]. If groups are matched on all variables, we will use independent t-tests (two-tailed) to compare T versus C groups on the primary long-term language outcome and the secondary short-term outcomes that relate to white matter development. Should groups not be balanced, and to account for missing data, we will use linear mixed models: T group as a fixed factor and unmatched or missing variables are random factors. Statistical significance is set at *p* < 0.05. Should an imbalance of twins or multiples occurs, we will perform group analyses including all singletons and one randomly selected twin or multiple from each set [58].

We will perform post hoc univariate and/or non-parametric analyses to determine if neural and clinical outcomes are associated with variations in the dose (i.e., number of hours of maternal speech delivered) or length (i.e., number of nights of delivery) of treatment, controlling for GA and PMA. Post hoc covariance analyses will permit further interpretation of either significant or non-significant treatment effects for short- and long-term neural and language outcomes. We will use multiple regression analyses to predict language outcomes from short-term neural and clinical outcomes, while controlling for group status and measures of language exposure.

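### The primary outcome is two unranked CDI scores, with an age range in the abstract and aim that differs from the Methods and no rule for success, so the primary error rate is not controlled

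*Protocol article*

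**What the plan says.** **Which scores.** Outcome assessment methods defines the primary outcome as the MacArthur-Bates CDI at 18 months adjusted age (AA), "quantified as expressive and receptive language raw scores and aggregated as group means". No composite is formed and neither score is put first. Analytic strategy then treats the outcome as singular: "we will use independent t-tests (two-tailed) to compare T versus C groups on the primary long-term language outcome".

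**Which age.**
- Study design: "At 18 months AA, parents will complete another CDI: Words and Gestures Questionnaire, the primary outcome assessment of language development". Outcome assessment methods agrees.
- Abstract, Methods: "The primary outcome will be measures of expressive and receptive language skills, obtained from a parent questionnaire collected at 12–18 months AA".
- Background, hypothesis for the first aim: "infants in the treatment group will demonstrate more advanced language skills at 12–18 months AA".
- The CDI subsection, under the primary-outcome heading, has the questionnaire completed "at 12 months AA and 18 months AA via web form or mail form".

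**Which error level.** Power calculations: "The significance level is *p* < 0.05 for all analyses". Analytic strategy repeats the 0.05 threshold. The article does not say whether one, either or both scores must reach it.

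**The concern.** The trial's main claim will be that maternal speech exposure does or does not improve later language. As written, that claim can rest on the expressive score, the receptive score, or both, and on the abstract's and aim's wording it can also rest on the 12-month questionnaire. Nothing in the article prevents the choice from being made after the results are known. A mixed result, with one score at p = 0.03 and the other at p = 0.40, could be reported as positive or negative, and each report would be compatible with the text.

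The sample size was derived for a single comparison at 0.05. Most ways of settling the two-score question change either the error rate or the power, so the power statement cannot be read as applying to the primary outcome until the rule is fixed.

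**Working it through.** **Inputs.** From Power calculations and Analytic strategy: 21 infants per group, two-tailed independent t-test, alpha 0.05, d = 1.0 (with d = 0.9 as the less favourable case). From Outcome assessment methods: two scores. From the CDI subsection: two ages. The correlations between scores and between ages are not given, so ranges are assumed: 0 to 0.9 between scores and 0 to 0.8 between ages.

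**Step 1: the plan's own figures.** Two-sided power is P(|T| > t₀.₉₇₅, 2n−2), where T is noncentral t with noncentrality d·√(n/2).
- d = 1.0, power 0.80: n = 16.7, so 17 per group (as stated); power at 17 is 0.807.
- d = 1.0, n = 21: 0.885 (stated 0.88).
- d = 0.9, n = 21: 0.812 (stated above 0.8).

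All three reproduce, and all three describe one test at 0.05.

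**Step 2: error rate if any significant score counts.** For k independent tests the rate is 1 − 0.95^k, which is 1 − 0.9025 = 9.75% for k = 2 and 1 − 0.8145 = 18.5% for k = 4. Counting only results that favour treatment (nominal 2.5%), it is 1 − 0.975² = 4.9% and 1 − 0.975⁴ = 9.6%. For correlated scores, two-sample t-tests with 21 per group were simulated under no effect (600,000 replicates, Monte Carlo standard error at most about 0.05 percentage points).

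| Tests that count | Assumed correlation (scores / ages) | Any two-sided p < 0.05 | Any result favouring treatment |
|---|---|---|---|
| Two scores, 18 months | 0 | 9.75% | 4.9% |
| | 0.5 | 9.1% | 4.5% |
| | 0.7 | 8.4% | 4.2% |
| | 0.9 | 7.1% | 3.6% |
| Two scores, 12 and 18 months | 0 / 0 | 18.5% | 9.6% |
| | 0.5 / 0.5 | 16.3% | 8.2% |
| | 0.7 / 0.6 | 14.5% | 7.2% |
| | 0.9 / 0.8 | 11.0% | 5.5% |

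**Step 3: error rate if both 18-month scores are required.** P(both significant) cannot exceed P(one given score significant), so 5% is a ceiling. With no effect on either score it is 0.05² = 0.25% at correlation 0 and 2.9% at 0.9.

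**Step 4: power at 21 per group under each possible rule, same d on both scores.**

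| Rule | d = 1.0 | d = 0.9 |
|---|---|---|
| One named score at 0.05 (also the first step of a fixed sequence) | 0.885 | 0.812 |
| Each score at 0.025 (Bonferroni; a lower bound for Holm), per score | 0.815 | 0.72 |
| Both scores at 0.05, correlation 0.5 to 0.7 | 0.81–0.82 | 0.70–0.73 |

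**The case against.** The strongest reply is that the Methods already settle the age. Both Study design and Outcome assessment methods say 18 months, and the latter is the formal outcome definition. The 12–18 month range sits in the abstract and the aim, which are summary text, and the CDI subsection does not call the 12-month form primary. This largely stands. A reader might infer that the plan treats four tests as primary, but the better-supported reading is two scores at 18 months. The 11–19% range shows only what the looser wording would permit.

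A reader might also infer that the false-positive rate is simply well above 5%. The document does not support that. It never says that either score alone suffices, so the rate is undefined until a rule is chosen. With both required it does not exceed 5%. For a claim of benefit on either of the two 18-month scores it is 3.6–4.9%, which is above the nominal 2.5% but not above 5%.

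Nor does any section propose pooling 12- and 18-month raw scores. That the scores are raw matters only in that the two ages are separate outcomes, so the age must be stated consistently.

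Finally, the choice of multiplicity method is often left to an analysis plan, and this is a condensed article. That is fair for the procedure itself. It does not cover an age conflict within the article, a primary outcome defined as an unranked pair, or an explicit 0.05 for every analysis. An analysis plan could not agree with all of these statements as they stand.

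**Conclusion.** The point holds: the primary age is stated inconsistently, the primary score is not singled out, and no success rule accompanies the blanket 0.05 level, so the error rate for the trial's main conclusion is not controlled. If any score may win, the two-sided rate is about 7–10% for the two 18-month scores and about 11–19% if 12 months is admitted. These ranges rest on assumed correlations, on a common d for the power figures, and on t-tests with all 21 infants per group contributing.

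The power figures are arithmetically correct, but they apply only if one score is tested at 0.05. The claim of power above 0.8 at d = 0.9 is the one most exposed: per-score power at 0.025, or power with both scores required, is roughly 0.70–0.73. Because this defines the primary conclusion, it should be settled before outcome data are analysed.

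**What to change.** 1. State 18 months AA as the single primary time point in the abstract and the first aim, as Study design and Outcome assessment methods already do, and label the 12-month CDI secondary.
2. Prespecify one rule for the two 18-month scores: (a) a fixed sequence with one named score first and the other tested only if the first is significant at 0.05; (b) Holm across the two; or (c) success only if both are significant at 0.05. Each holds the two-sided error for the pair at or below 5%.
3. Match the power statement to the rule.

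**Cost.** Steps 1 and 2 are wording. Under (a), the first score keeps 0.885 and 0.812. Under (b), per-score power is at least 0.815 at d = 1.0 and 0.72 at d = 0.9. Guaranteeing 80% per score at 0.025 needs 21 per group (20.3 rounded up) at d = 1.0, which is the planned size, but 25 (24.8 rounded up) at d = 0.9. Under (c), power is about 0.81–0.82 and 0.70–0.73 at assumed correlations of 0.5–0.7. If (b) or (c) is chosen, the statement that power exceeds 0.8 at d = 0.9 should be replaced by the figure for that rule.

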### Primary outcome: language development

#### MacArthur-Bates CDI

In order to measure language development and production, parents of infant participants will complete the CDI: Words and Gestures Questionnaire [46] at 12 months AA and 18 months AA via web form or mail form with guidance from a trained clinical research assistant. The CDI Words and Gestures Questionnaire is a parent checklist that evaluates both verbal and non-verbal communication, as well as some aspects of play. Split into two parts, “The Early Words” section examines infants’ intentional linguistic communication, understanding, vocabulary, and language-based social interactions, while the “Actions and Gestures” section gauges communicative gestures, play, and symbolic understanding. As these metrics of language development are related to measures of processing speed and predictive of later language outcomes, the CDI Words and Gestures Questionnaire will serve as our primary measure of language development.

### Secondary outcomes: white matter development

#### Scanning procedures

At each age point, dMRI scans will be collected on a 3-T MRI (GE-Discovery MR750) using multi-slice scanning. The MRI scanning duration is approximately 30 min. Sequence parameters are optimized for neonates and infants and are constant across age points. Neonatal scans will be performed at LPCH as part of the routine medical care prior to hospital discharge. Infant scans will be collected at the Center for Cognitive and Neurobiological Imaging at Stanford. We follow established procedures to ensure safety and successful scan acquisition (e.g., scanning at bedtime, noise-canceling headphones, swaddling to reduce movement) [47].

#### Diffusion MRI parameters

We will collect two dMRI scans that vary in terms of b-values (700 s/mm^2^ and 1500 s/mm^2^). Each scan is collected at 2.0 mm^3^ spatial resolution with full-brain coverage and 60 non-collinear directions. Six volumes are acquired at b = 0. We employ a multi-slice echo-planar imaging (EPI) protocol to ensure rapid image acquisition (~ 3 min). To correct for EPI distortions, we collect an additional short scan with 6 non-diffusion-weighted volumes with reversed phase encoding (posterior-anterior). The rationale for a low b-value (b = 700) is to optimize the signal-to-noise ratio for measuring diffusion in the underdeveloped neonate brain. We will also collect a high-resolution T1-weighted scan for anatomical reference. We use a 3D fast spoiled gradient sequence.

#### Neuroimaging pre-processing and tractography

We plan to use established pipelines for image pre-processing and tractography. These pipelines rely on a combination of open-source software, including mrDiffusion [48], Statistical Parametric Mapping [49], FMRIB Software Library [50], mrTrix3 [51], Advanced Normalization Tools [52], and Automated Fiber Quantification [53]. Pre-processing includes the alignment to T1-weighted anatomical scan, de-noising, and corrections for participant motion, eddy currents and EPI distortions, and model fitting to obtain the three eigenvalues (λ1, λ2, λ3) used to compute MD, FA, radial diffusivity, and axial diffusivity. Tractography procedures include steps for producing the whole-brain tractogram, segmentation of individual white matter fiber groups in native space, and estimation of diffusivity metrics within specified tract segments [53].

#### Control variables and covariates

To characterize the sample and ensure balance across groups in analyses for treatment effects, we will prospectively collect the following information from electronic medical records and parent report questionnaires to control for (1) major medical complications associated with prematurity, including GA, birth weight, sex, history of antenatal steroid usage, infection, number of days of intubation and oxygen, and X-ray changes consistent with chronic lung disease; (2) PMA at MRI scan; (3) the number of nights of exposure to study treatment; and (4) sociodemographic factors associated with later language outcomes, including the SES of primary caretakers as measured by the HI [43], the frequency and number of languages spoken by adult and child household members, and number of siblings.

We will also obtain metrics to ensure balance across groups on the basis of the amount of language exposure experienced by infants in their home environments. To collect data on naturalistic maternal/caregiver input during the infancy period, we plan to use the Language ENvironment Analysis (LENA) recording device and software [54]. Families will be asked to perform two full-day (16 h) home LENA voice-recording sessions immediately around the time of the 12 months AA visit for MRI scanning. From this device, we will examine the adult words count measure per hour, normalizing for the length of audio recording, since it is the most accurate measure from LENA at this age when the infants may have limited language production skills [55]. If the groups do not match, we will use this language exposure metric as a covariate in the analyses.

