#### Delivery of intervention

The intervention will occur for a minimum of 2 weeks (28 h) and a maximum of 9 weeks (126 h) prior to the date of the clinical brain imaging scan. Neonates randomized to the T group (maternal speech group) will listen, via an iPod placed in cribs and/or incubators, to recordings of their mother’s speech at hourly intervals between 10:00 p.m. and 6:00 a.m. Administration of the intervention during periods when parents are unlikely to visit the hospital is expected to minimize parental knowledge for the group assignment. Recordings will be played automatically using the alarm function to avoid reliance on clinical staff. Research staff will regularly check on the status of the device to ensure proper functioning. Neonates will hear a total of 2.67 h of speech recordings per night (20 min/h × 8 h). Treatment length will be defined as the number of nights from the start of treatment (i.e., beginning of PICN stay) to the end of treatment (i.e., date of MRI scan at 36–38 weeks PMA). Within a given hour, two 10-min segments will be randomly presented to avoid synchronization with biological and sleep rhythms. Sound intensity for speech recordings is balanced between open cribs versus incubators and is below hourly NICU safety levels less than 50 dB [45].

Neonates in the C group will receive standard care. All infants in the NICU receive developmental care support from health care providers and families, and clinical staff tracks which activities are experienced by all infants through nursing documentation. Clinical staff uses a standard care path to guide which types of activities are appropriate for an infant depending on the maturity and health status. Families are generally encouraged to talk, read, and sing to their infants when visiting, if the infant is deemed in the appropriate stage. Auditory setup will be the same for neonates in the C group; however, these neonates will not hear speech recordings. This procedure ensures that parents remain blinded to the group randomization.

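### PMA at MRI scan is listed as a control variable, but the analysis plan gives no proper adjustment for it in the MD comparison, which costs precision on a secondary outcome

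*Protocol article*

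**What the plan says.** All references are to the protocol article.

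- **Control variables and covariates** names "2) PMA at MRI scan" as the second group of variables collected for control and for group balance when treatment effects are analysed.
- **Analytic strategy** sets balance checks "on the basis of GA, sex, SES, clinical complications associated with premature birth, and language exposure during treatment and after hospital discharge". Scan age is not named.
- The same section then fixes the default test: "If groups are matched on all variables, we will use independent t-tests (two-tailed) to compare T versus C groups". This covers the primary language outcome and the short-term white matter outcomes. Otherwise, a linear mixed model is used, with group as a fixed factor and unmatched or missing variables as random factors.
- PMA appears as a control only in the post hoc analyses of the dose or length "of treatment, controlling for GA and PMA".
- **Delivery of intervention** ends treatment at the "date of MRI scan at 36–38 weeks PMA", so the neonatal scan falls in a window and not at one fixed age.
- **Randomization and RCT design elements** applies minimisation to GA stratum and SES. Scan timing is not controlled by allocation.

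**The concern.** MD is used here as a marker of maturation: the Background section expects lower MD in the treated arm and places the first measurement at roughly 36 weeks PMA. If MD changes with age over the scan window, part of its spread between infants is simply age at scan. An unadjusted comparison leaves that spread in the error term, and if one arm happens to be scanned earlier, the observed difference carries some of that age gap.

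The article treats scan age as worth controlling in its list of control variables and PMA as worth controlling in the post hoc dose analyses, but not in the randomised MD comparison. The two sections need to be reconciled. At stake are the precision of a secondary outcome and how the single observed contrast is read.

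**Working it through.** **Inputs from the article.** 21 infants per arm; design effect d = 1.0, with d = 0.9 as the smaller scenario; two-tailed t-test; "The significance level is *p* < 0.05 for all analyses".

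**Inputs assumed.** The correlation ρ between MD and PMA at scan is not given, so a range is shown. All 42 infants are taken to contribute a usable, independent neonatal MD value, the relation of MD to age is linear, and treatment does not change scan age.

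**1. Reproduce the stated power.** For an unadjusted two-sided t-test, the noncentrality is d × √(n/2) with 2n − 2 df.
- n = 21, d = 1.0: 1.0 × √10.5 = 3.24, 40 df, power 0.885 (stated 0.88).
- n = 17, d = 1.0: power 0.807 (stated 0.8).
- n = 21, d = 0.9: power 0.812 (stated above 0.8).

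The stated figures are right, and they rest on the unadjusted test.

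**2. How large a scan-age difference passes a balance test?** The standard error of the between-arm difference in mean scan age is √(2/21) = 0.309 SD. The test becomes significant only beyond t(0.975, 40) × 0.309 = 2.021 × 0.309 = 0.62 SD. If scan age were uniform over 36–38 weeks (an assumption), its SD would be 2/√12 = 0.58 week, and 0.62 SD would be 0.36 week, or about 2.5 days.

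A difference at that limit shifts the standardised MD contrast by ρ × 0.624: 0.19 at ρ = 0.3, 0.31 at 0.5 and 0.37 at 0.6. A one-standard-error difference shifts it by ρ × 0.309: 0.09 at 0.3 and 0.19 at 0.6. These shifts are part of the contrast's existing sampling error, not an addition to it.

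**3. Type I error of the unadjusted test.** Simulation under no treatment effect (40,000 trials for each ρ):

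| ρ | Overall | Given scan-age difference 0.5–0.62 SD | Given difference below 0.1 SD |
|---|---|---|---|
| 0.3 | 0.051 | 0.075 | 0.042 |
| 0.5 | 0.049 | 0.100 | 0.026 |
| 0.7 | 0.051 | 0.163 | 0.008 |

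The overall rate is held. It is too high when the arms differ in scan age and too low when they agree.

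**4. Power with scan age as a fixed covariate.** The variance ratio is (1 − ρ²) × 39/38, where 39/38 allows for chance covariate imbalance. The noncentrality is d × √10.5 divided by the square root of that ratio, with 39 df. Equivalent n is 21 divided by the ratio.

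| ρ (assumed) | Variance ratio | Equivalent n per arm | Power, d = 1.0 | Power, d = 0.9 |
|---|---|---|---|---|
| Unadjusted t-test | 1 | 21 | 0.885 | 0.812 |
| 0 | 1.026 | 20.5 | 0.877 | 0.802 |
| 0.2 | 0.985 | 21.3 | 0.889 | 0.817 |
| 0.3 | 0.934 | 22.5 | 0.905 | 0.837 |
| 0.5 | 0.770 | 27.3 | 0.950 | 0.900 |
| 0.6 | 0.657 | 32.0 | 0.974 | 0.939 |

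Adjustment reduces variance once ρ² exceeds 1/39, that is, |ρ| above about 0.16.

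**The case against.** **The plan may already cover it.** The t-test applies only if the groups match on all variables, and that can be read to include the whole list under Control variables and covariates. A reader might infer that the plan ignores scan age altogether; the text does not support that much. On the wider reading, however, scan age comes in only when a significance test flags it, and then as a random factor. The same article speaks of using home language exposure as a covariate if the groups do not match, so its two sections differ on method as well.

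**Randomisation protects the comparison.** A reader might infer that the unadjusted test is biased or has inflated type I error. It is neither: chance differences in scan age are already in the standard error, and the overall rate stays at 0.049–0.051. The harm is conditional on the imbalance that occurs, as for any prognostic covariate.

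**Scan age is measured after randomisation.** The Background cites effects of maternal speech on weight gain and feeding tolerance. A reader might infer that one arm will reach discharge, and hence the scan, sooner. Nothing in the article shows this. If it happened, the adjusted and unadjusted contrasts would answer different questions. This stands as a condition on the fix: the target must be stated and both contrasts shown.

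**The covariate set may sit in a fuller document.** That would be fair if the article were silent. It is not: it names the test, the balance list and the fallback, and the point concerns those statements.

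**The gain depends on an unknown correlation.** This also stands; below about 0.2 there is little to gain.

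**Conclusion.** The point holds as a mismatch between two sections and an avoidable loss of precision on a secondary outcome. Neither reading of the Analytic strategy gives an ordinary covariate adjustment for scan age. With 21 per arm and an assumed correlation of 0.3 to 0.6, power would rise from 0.885 to 0.905–0.974 at d = 1.0 and from 0.812 to 0.837–0.939 at d = 0.9. The gain is negligible near 0.2, and the cost is about 0.01 at zero.

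The stated power is correct, the randomised contrast is valid on average, and the primary language outcome is unaffected. The change is worth making because it is cheap, but the trial's validity does not depend on it.

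**What to change.** In the Analytic strategy, replace the conditional t-test for neonatal MD with a pre-specified linear model, used whatever the balance tests show: treatment and PMA at scan as fixed terms, plus the two minimisation factors (GA stratum and SES). Use the same form for 12-month MD, with adjusted age at scan in place of PMA. Bring the list under Control variables and covariates into line with it.

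Because scan age is measured after randomisation, report it by arm, keep the unadjusted contrast as a sensitivity analysis, and state that the adjusted contrast targets MD at a given age.

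No new data are needed for the neonatal model, since PMA at scan is already to be collected. The price is one degree of freedom for scan age and two for the binary minimisation factors, leaving 42 − 5 = 37 residual df instead of 40. The power figures above charge only for scan age.
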